### Activity coaching system in the intervention group

The home-based program is exactly the same for the intervention and the control group. The only difference is the addition of the digital activity coaching system in the intervention group. The intervention group wears the activity coaching system during the home-based exercise program for two weeks: After two weeks’ use, the influence of the activity coaching system seems to diminish because patients include exercises in daily routines as shown in patients with COPD [27]. Physical therapy after TKA is effective when it starts early [29], so we hypothesize that adding the activity coaching system in the first two weeks [30, 31] stimulates people towards a more active and healthy activity behaviour. It consists of an accelerometer-based activity sensor (Promove 3D, Inertia Technology, Enschede, the Netherlands), which is worn on the patient’s hip combined with a smartphone (Desire S; HTC, New Taipei, Taiwan). The activity coaching system is shown in Fig. 2 and consisted of a tri-axial piezoelectric accelerometer. The accelerometer measures accelerations in the anteroposterior, mediolateral and longitudinal axis of the trunk. The acceleration is band pass filtered, with cut-off frequencies at 0.11 and 20 Hz as described by Bouten et al. [32] and is used to remove the gravitational component from the accelerometer signals. These filtered signals are used to calculate the Integral of the Modulus of the Accelerometer output (IMA) values for the most recent 60 s. The IMA values as measure for physical activity are expressed as mean acceleration per minute and defined as counts per minute [32].

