**Methods:**

This study is a single-blind randomized controlled trial. Both the intervention (*n* = 55) and the control group (*n* = 55) receive a two-week home-based exercise program, and the intervention group receives an additional activity coaching system. This is a hand-held electronic device together with an app on a smartphone providing information and advice on exercise behavior during the day. The primary outcome is physical functioning, measured with the Timed Up and Go test (TUG) after two weeks, six weeks and three months. Secondary outcomes are 1) adherence to the activity level (activity diary); 2) physical functioning, measured with the 2-Minute Walk Test (2MWT) and the Knee Osteoarthritis Outcome Score; 3) quality of life (SF-36); 4) healthcare use up to one year postoperatively and 5) cost-effectiveness. Data are collected preoperatively, three days, two and six weeks, three months and one year postoperatively.

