## Methods

### Study design

The study design is a single-blinded parallel superiority RCT. The flow chart is shown in Fig. 1. Postoperative measurements take place at the beginning of the home-based exercise program, after two weeks, after six weeks, after three months and after one year. The outcome measures are performed by one researcher, who is blinded to the group assignment.

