### Randomization, blinding and treatment allocation

The orthopedic surgeon checks the inclusion criteria after surgery for definitive inclusion. To assign participants to either of the groups a randomization list is generated by a computer (www.randomization.com) using block randomization with a block size of 6. Pre-stratification is applied for the level of physical activity determined with the activity coaching system prior to surgery (< the median level or ≥ the median level). The median activity level was determined in a pilot of 10 consecutive patients. An independent secretary not involved in enrolling participants in the study prepares concealed, consecutively numbered, sealed, opaque envelopes. The envelopes contain papers indicating the allocated treatment. Participants will receive their envelope at the start of the home-based exercise program from another independent secretary who is not aware of the randomization sequence. Participants can open the envelope while with the physical therapist. Subsequently, the physical therapist will inform the trial coordinator (KH) about the treatment allocation. Patients are instructed not to tell the researcher which group they are randomized to during the follow-up measurements.

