### Home-based exercise program

Patients in the intervention group and control group both receive a home-based exercise program. A trained physical therapist experienced in the treatment of patients after TKA and trained in the home-based exercise program explains the program to the patients. There are at least two contact moments: at the start of the program, to give exercise instructions and feedback on the correct performance, and at the end of the program, to monitor the effectiveness. When in need of help the patient is allowed to consult the therapist. The program is explained face to face at the patients’ home immediately after their hospital stay and the exercises are practiced with the patient to be sure that they are done correctly. The program consists of cycling on a home trainer, outside walking and some exercises to improve range of motion (ROM) and muscle strength. The program is shown in Table 1. The home-based exercise program is followed for two weeks and patients are asked to perform the exercises at least five times a day with a gradual increase in time and speed within the two weeks. Patients receive a home trainer for two weeks to do their cycling exercises. Apart from the home-based exercise program patients are allowed to do extra walks or extra daily activities if they want and are able to do so. They are instructed to avoid strenuous activities such as playing football or other sports activities*.* Patients are informed that they can contact the physical therapist if they need consultation and are allowed to receive other kinds of care (e.g. help in the household). There is no limit on the number of consultations needed, because patients need to be sure that they do their exercise adequately. Healthcare use (including physical therapy consultations) is compared between the intervention and the control group.

**Table 1 Tab1:** exercise program

Week 1	
Day 1	• Explaining home-based exercise program through physical therapist
	• All exercises were explained
Day 2	• Cycling on a hometrainer 2 × 10 min
	• Walking outside 2 × 15 min
	• RoM exercises knee 15 min
Day 3	• Cycling on a hometrainer 2 × 10 min
	• Muscle strength exercises quadriceps 15 min
	• Walking up and down stairs 5 min
	• Walking outside 15 min
Day 4	• Hometrainer 1 × 10 min and 1 × 15 min
	• Walking outside 2 × 15 min
	• RoM exercises knee 15 min
	• Muscle strength exercises quadriceps 15 min
Day 5	• Hometrainer 1 × 10 min en 1 × 15 min • Walking outside 2 × 15 min

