### Secondary outcomes

Secondary outcomes are divided into adherence to the activity level (activity diary), performance-based physical function (2MWT), self-reported physical function (KOOS), quality of life (SF-36) and healthcare use.Adherence to the activity level measured with the activity diary

Activity level was defined as the type of activities performed and the time spent on it. Because of the absence of a valid and reliable activity-level questionnaire for patients after a TKA an activity diary was developed. The activity diary focuses on physical activities and there is low burden to administer. Every day patients report which activities they have performed and for how many minutes. Walking, cycling, exercises, walking up and down stairs, household chores, pastime and leisure activities, work and sports activities are mentioned in the activity diary and the patient has the opportunity to note other activities and the time spent on them. Other authors used similar activity diaries in healthy adults [36–38]. The activity diary must be filled out one week preoperatively, during the home-based exercise program, in the sixth week, in the third month and one year after surgery (during one week). The minutes spent on each type of activity will be compared to the recommended time per activity as defined in the home-based exercise program (Table 1) to calculate the percentage of adherence (this can be lower or higher than 100%).Performance-based physical function measured with the 2MWT

The 2MWT measures walking speed. The outcome is the distance in meters. The 2MWT record on a smooth floor with sufficient walking space over a distance of 10 m. The measurements take place at the patients’ home and therefore 10 m was determined as standard because this is the maximum available space at home. The patients have to walk as many meters as possible in two minutes. They are allowed to use a walking aid [39]. The 2MWT is performed after two and six weeks and three months. During the preoperative 2MWT the Gait Analysis List Nijmegen is used to measure the quality of the gait pattern.Self-reported physical function, measured with the Knee Osteoarthritis Outcome Score (KOOS)

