The KOOS assesses function over the previous week and is composed of five subscales: pain, symptoms, activities in daily living, activities in sports and leisure, and knee-related quality of life [40–43]. Answers are given using a Likert scale ranging from 0 to 4. A normalized score (100 indicates no symptoms, and 0 indicates extreme symptoms) is calculated for each subscale. The KOOS has been shown to have excellent reliability and good content and construct validity when used for short- and long-term follow-up of knee injury [42, 43]. It has been validated for people with TKA and has been used to evaluate physical therapy outcomes [42, 43]. The KOOS is scored after two and six weeks, three months and one year.Quality of life (QoL), measured with the Short Form 36 (SF-36)

The SF-36 is a multipurpose, short-form health survey with 36 questions that measure eight domains of QoL (vitality, physical functioning, bodily pain, general health perceptions, physical role functioning, emotional role functioning, social role functioning and mental health). It has been shown to capture improvements in seven of its eight domains in patients after TKA in the first three months after surgery [44] and continues to indicate improvements in health-related QoL over the next six months [45]. In addition, the results of the eight domains have been combined into two summary scores: physical component score and mental component score [46]. The SF-36 is scored after two weeks, six weeks, three months and one year postoperatively.Healthcare use

Healthcare use includes all kinds of healthcare consumed by the patient in relation to TKA surgery beginning at the start of the home-based exercise program up to one year postoperatively. It includes physical therapy, hospital visits, visits of the general practitioner and medication use. The patient sign informed consent to ask for an overview of healthcare costs (health insurance, physical therapist) and patients report how much pain medication (paracetamol, NSAIDs) they use for their knee pain. The use of pain medication is asked about through a medication diary. Healthcare use is measured during the period up to one year after surgery.Adherence to the home-based exercise program (intervention group) measured with the accelerometer (activity coaching system)

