### Interviews

Every third patient who receives the activity coaching system will be asked to participate in a qualitative semi-structured interview to determine the usability of the activity coaching system. Semi-structured interviews with the patients will be conducted three months after surgery. The interviews will take place at the patients’ home and the duration of the interview is at most 30 min. The interviews will be conducted by an independent researcher not involved in the measurements or treatments to guarantee independence. Inclusion of patients will be stopped if saturation is reached (no new information in the last three interviews).

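### The two-week visit has no consistent time origin; if it is counted from surgery, the first primary TUG falls before device wear ends and puts the assessor's blind at risk

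*Protocol article*

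**What the plan says.** All references are to the protocol article.

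**Program and device.** Home-based exercise program: "The home-based exercise program is followed for two weeks". It is explained at the patient's home directly after the hospital stay, and Table 1 runs from Day 1 to Day 14. Activity coaching system in the intervention group: "The intervention group wears the activity coaching system during the home-based exercise program for two weeks". The system is a hip-worn sensor with a smartphone that sends messages during the day. After surgery only the intervention arm uses it.

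**Start.** Procedures and informed consent places definitive inclusion at discharge, three days after surgery. Baseline is preferably on day 3 and no later than day 5, and randomization follows definitive inclusion.

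**Visit timing.** Abstract, Methods: "Data are collected preoperatively, three days, two and six weeks, three months and one year postoperatively". The hypothesis at the end of the Background also counts two weeks from surgery, and Secondary outcomes says: "The SF-36 is scored after two weeks, six weeks, three months and one year postoperatively". Study design instead opens its list of postoperative measurements with the start of the home program and then gives two weeks, six weeks and so on. Objective and Primary outcome name two weeks, six weeks and three months for the TUG without an origin.

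**Blinding.** Study design: "The outcome measures are performed by one researcher, who is blinded to the group assignment". Randomization, blinding and treatment allocation: "Patients are instructed not to tell the researcher which group they are randomized to during the follow-up measurements". Under the 2MWT in Secondary outcomes: "The measurements take place at the patients’ home".

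**The concern.** The first primary time point can be read in two ways, and the two readings differ in substance. On one, the visit falls inside the period of device wear. On the other, it falls just after.

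If it falls inside, two things follow. First, the assessor may meet a visible device that exists in one arm only. An instruction not to speak about allocation does nothing about a sensor on the hip or a study phone on the table. Any loss of blinding would be one-sided, and the same researcher returns at six weeks and three months, so it could carry over to the other two primary time points. Patients are not blinded (Abstract, Discussion) and the TUG is performed as fast as the patient safely can, so assessor blinding is the main protection the design has against measurement bias.

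Second, the visit would describe patients part-way through the program and still being messaged, among other things about how to load the leg in transfers and walking. A reader of the results would need to know that.

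**Working it through.** The plan gives no figure of its own for this overlap, so the check is calendar arithmetic from its stated days.

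**Inputs**
- Program length 14 days (Table 1), with the device worn throughout (Activity coaching system section).
- Program start on postoperative day (POD) 3 to 5. This is an assumption drawn from discharge on day 3, baseline on day 3 to 5, and the envelope being handed over at program start. The start day counts as program day 1.

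**Formulas**
- Last program day = start + 13.
- Program day on POD 14 = 14 − start + 1.
- Program days still to come after POD 14 = (start + 13) − 14.
- Visit two weeks after program start = start + 14.

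| Program start | Last program day | Counted from surgery: POD 14 is | Program days left | Counted from program start: visit on |
|---|---|---|---|---|
| POD 3 | POD 16 | program day 12 | 2 | POD 17 |
| POD 4 | POD 17 | program day 11 | 3 | POD 18 |
| POD 5 | POD 18 | program day 10 | 4 | POD 19 |

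**Program content still to come.** Adding the Table 1 minutes per day gives 65, 55, 85, 85, 85, 75, 105, 100, 100, 100, 100, 130 and 130 for days 2 to 14, a total of 1215. Day 1 is instruction only.
- Start on POD 3: days 13 and 14 remain, 130 + 130 = 260 minutes; 260/1215 = 21%.
- Start on POD 5: days 11 to 14 remain, 100 + 100 + 130 + 130 = 460 minutes; 460/1215 = 38%.

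The remaining days include the two heaviest of the program.

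**Reach.** On the surgery origin, one of three primary time points is affected directly, in up to all 55 intervention patients. Suppose assessor knowledge shifted the measured difference by b seconds at that visit only, and the three follow-ups were weighted equally. The average effect would then move by b/3. If the shift carried over to all three visits, it would move by b. The documents give no basis for a value of b.

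On the program-start origin, no program days remain at the visit and the overlap disappears.

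**The case against.** The strongest reply is that Study design is the Methods text on measurement timing, and its list starts at the beginning of the home program. It is natural to count the next two weeks from there, which puts the TUG after program day 14. The flow chart, which is not shown, may settle the matter. This stands to the extent that the overlap cannot be stated as fact. It does not remove the inconsistency: the Abstract, the Background hypothesis and the SF-36 text count from surgery, and the primary outcome definition is silent.

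A second reply is that measuring during treatment is not in itself an error. The primary analysis is an overall GEE effect, and the six-week and three-month visits lie after wear on either reading. That is right, and the incomplete exposure is the lesser part of the point.

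A third is that handling the device at visits is operational detail that an article may leave to the full protocol. That is fair for a missing return procedure alone. Here, however, the stated timing can itself place the visit inside the wear period, with only a verbal safeguard written down.

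Some stronger readings are tempting, but the article does not support them:
- **The assessor is unblinded.** Nothing says the sensor is worn during testing, and patients log when they put it on and take it off. The home setting is stated only under the 2MWT.
- **The three-month device interviews also threaten the blind.** "Semi-structured interviews with the patients will be conducted three months after surgery", but the Interviews section assigns them to an independent researcher not involved in measurement or treatment.
- **The largest effect is expected at two weeks, or the test is hand-timed.** Neither is stated. Sample size assumes a mean difference over time.

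**Conclusion.** The point holds in conditional form. The origin of the two-week visit is inconsistent within the article and undefined for the primary outcome. If it is surgery, the first primary TUG comes 2 to 4 days before the program and device wear end, on program day 10 to 12. The blinded assessor may then see equipment that only one arm has, and the stated safeguard does not cover that. If it is program start, the visit falls on POD 17 to 19 and the overlap is gone.

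This rests on a program start between POD 3 and POD 5 and on the TUG being done at home like the 2MWT, by the same researcher. The direction and size of any bias cannot be derived from the documents. The sample size is not affected. It is a worthwhile, inexpensive improvement rather than a flaw that invalidates the primary comparison.

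**What to change.** 1. Name one time origin for all follow-up visits and use it in the Abstract, Background, Objective, Study design, Primary outcome and Secondary outcomes.
2. Schedule the first follow-up assessment just after program day 14.
3. State that the sensor and smartphone are handed back at the end-of-program contact with the physical therapist, and that the assessor visits only after that.

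This is a wording and scheduling change. The end-of-program contact already exists, so it needs no extra visit or staff. The downside is that the first follow-up moves from POD 14 to about POD 17 to 19 for any patient who would have been seen on the surgery origin.

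The stated recruitment period ends on 1 August 2017, shortly after publication. For patients already assessed, the practical step is to state which origin was used and to tabulate by arm the program day on which the visit took place.

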**Fig. 2 Fig2:**
[figure not shown]
Activity coaching system, consisting of a smartphone and an accelerometer based activity sensor

The smartphone application shows two lines: the activity line (in counts per minute) and the reference activity line (in counts per minute). The activity line (displayed on the screen as a blue line) shows the distribution of activities during the day, the intensity of the activities and the duration of the activities. The reference activity line is the cumulative activity the patient should aim for (displayed on the screen as a green line). The reference activity line represents an even distribution of activity intensity during the day. The cumulative activity level represented by this reference line is based on the average cumulative activity level of a previously recorded group of healthy subjects [33].

Patients receive visual feedback in a graph displaying the cumulative reference activity line together with the activity line of the patient drawn minute by minute. Besides that the system coaches towards a healthy activity pattern by providing time-based motivational cues in the form of messages on a smartphone during the day for creating both awareness (how active was the patient up to that moment in time) and extra motivation (remember messages such as go cycling, walking or doing exercises). In addition, text messages contain advice on how to use the affected leg (e.g. symmetric load during transfers and walking). Feedback messages are based on the activity level of the last two hours and of the day so far. They provide a summary of the activity behaviour and advice on how to continue it, i.e. to do more or less to gain their reference activity level.

### Baseline characteristics of participants

Evaluation of baseline characteristics provides insight into the generalizability of the study, the success of the randomization and any potential confounders. Baseline characteristics of participants collected preoperatively are: age (years), gender, BMI, activity level (activity diary), coping style (PAM), walking pattern (GALN), physical status (TUG, 2MWT, KOOS) and quality of life (SF-36). This is shown in the flow chart (Fig. 1).

### Primary outcome

The primary outcome is the between-group difference in physical functioning as measured by the TUG after two weeks, six weeks and three months. The TUG measures the time it takes a patient to rise from an armchair (seat height of 46 cm), walk 3 m, turn, and return to sitting in the same chair without physical assistance [34]. Patients are instructed to walk safely, but as fast as they can. This test has excellent interrater (ICC 0.97) and intrarater reliability (ICC 0.96), as measured in a group of 65 subjects (aged 45–70) with knee osteoarthritis [34]. The TUG has also been shown to be responsive to change after TKA [35]. The TUG is recorded twice and the highest score of the two measurements is analyzed.

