### Sample size

The sample size is based on the primary outcome measure TUG. The sample size is determined using a longitudinal regression model with three follow-up measurement points (two and six weeks and three months). According to the formula described by Twisk [48] for longitudinal studies with repeated measures the required sample size is calculated assuming a mean effect of 10% difference for the TUG scores between the groups over time and a standard deviation of 4.2. These parameter values are based on a study by Kennedy et al. on the clinimetric properties of the TUG in patients with knee and hip arthroplasty [35]. We further assume a correlation coefficient of 0.4 for the correlation between the follow-up measurements. Assuming a dropout rate of 15% a total number of 110 patients is needed. The recruitment period is from 1 April 2015 to 1 August 2017.

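### Analysing the highest of two TUG scores selects the slower attempt, because the TUG is a time; the primary outcome rule must say which time is meant

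*Protocol article*

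**What the plan says.** The Primary outcome section describes the scale first: "The TUG measures the time it takes a patient to rise from an armchair", walk 3 m, turn and sit down again. The instruction follows: "Patients are instructed to walk safely, but as fast as they can". The section closes with the selection rule: "The TUG is recorded twice and the highest score of the two measurements is analyzed".

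This value carries the trial's main result: "The primary outcome is the between-group difference in physical functioning as measured by the TUG after two weeks, six weeks and three months". The TUG is also the basis of the Sample size section. Under Statistical analysis (Primary and secondary outcomes) it is the variable in the primary GEE model, with measurements at baseline, two weeks, six weeks and three months. It is also listed among the preoperative characteristics.

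**The concern.** On a timed test a larger number is a worse result. A rule that keeps the highest of two times keeps the slower attempt and discards the better one, although the patient was asked for maximal safe speed. There are two possibilities:

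- The authors mean the slower attempt. The choice is then unusual, and the article gives no reason for it.
- The authors mean the best attempt. The rule then states the reverse.

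The second is easy to imagine. On other outcomes in the same article higher is better: the 2MWT is a distance in metres, and a KOOS of 100 means no symptoms.

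The definition of the primary endpoint is at stake. Two analysts could compute it in opposite directions, each believing that the protocol was followed, and reported TUG levels could not be interpreted without knowing which time was used. This is not a detail left to an analysis plan, because the article states a rule and that rule conflicts with its own scale and instruction.

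**Working it through.** No figure in the article depends on this rule, so there is none to reproduce. The check is a reading, followed by a calculation of size.

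**Reading.** The scale is a time, so lower is better. The instruction is to go as fast as is safe. The rule keeps the highest value, so it keeps the slower attempt. The article nowhere converts the TUG to a speed, reverses the scale, equates highest with best, or gives a reason for using the slower attempt.

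**Inputs.**
- SD 4.2 s, from the Sample size section ("assuming a mean effect of 10% difference for the TUG scores between the groups over time and a standard deviation of 4.2"), taken as the SD of a single attempt.
- Intrarater ICC 0.96, from the Primary outcome section. Treating it as the agreement between two attempts at one visit is an assumption; 0.90 and 0.80 are added as assumed lower values.
- Attempt errors are taken as normal and independent.

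**Gap between the two attempts.** The within-patient SD is s = SD × √(1 − ICC), and the expected slower-minus-faster gap is 2s/√π.

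| ICC | s (s) | Expected gap (s) |
|---|---|---|
| 0.96 | 4.2 × √0.04 = 0.84 | 0.95 |
| 0.90 | 4.2 × √0.10 = 1.33 | 1.50 |
| 0.80 | 4.2 × √0.20 = 1.88 | 2.12 |

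**Precision.** The error variance is (1 − 1/π)s² = 0.682s² for the maximum, the same for the minimum, and 0.5s² for the mean. With ICC 0.96, the between-patient variance is 4.2² × 0.96 = 16.93 and s² = 0.706.
- Maximum or minimum: 16.93 + 0.48 = 17.42 after rounding, SD 4.17 s.
- Mean of two: 16.93 + 0.35 = 17.29 after rounding, SD 4.16 s.

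The variance ratio is 17.42/17.29 = 1.007, a difference of 0.7%. At an assumed ICC of 0.80 the simulated SDs are 4.06 and 3.98 s, a variance difference of about 4%.

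**Effect on the group comparison.** The average gap is the same in both arms and cancels, which leaves only chance movement. The SD of one patient's gap is s × √2 × √(1 − 2/π) = 0.84 × 0.853 = 0.72 s. Take errors as independent across the three follow-up visits and 110 × 0.85 = 93.5 evaluable patients, or 46.75 per arm. Switching from the slower to the faster time then moves the between-arm estimate with an SD of (0.72/√3) × √(2/46.75) = 0.09 s (0.19 s at ICC 0.80).

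For comparison, the standard error of the estimate uses the article's correlation of 0.4 over three visits. The variance factor is (1 + 2 × 0.4)/3 = 0.60, so the standard error is 4.2 × √0.60 × √(2/46.75) = 0.67 s.

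**The case against.** Taken literally, the highest of two times is a definite, prespecified rule. Analysing the slower attempt is unusual but not invalid. The instruction governs how each attempt is performed and does not by itself settle which one is analysed. One researcher, blinded to allocation, performs the outcome measures (Study design), so drift in the rule between assessors is unlikely. All of this stands, and it limits the consequences. It does not remove the conflict between rule and scale, and the article gives no reason that would show the slower time to be deliberate.

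A reader might infer more from the size of the gap, in three ways:

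- **That 0.95 s is about half of what the trial can detect.** The article states neither power nor the mean to which its 10% applies, so a detectable difference has to be assumed: about 1.9 s at 80% power or 2.18 s at 90%, with two-sided 0.05 and 15% dropout. The comparison also misleads, because the gap is a level shift shared by both arms whereas the detectable difference is a contrast between them.
- **That the treatment comparison is biased.** The same rule applies to both arms under a blinded assessor. A bias would need attempt-to-attempt variability or learning to differ by arm, and the article offers no evidence of that.
- **That the maximum costs power.** The faster time has the same variance as the slower under the normal model, and the mean improves total variance by under 1% at ICC 0.96.

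**Conclusion.** The point holds as a defect in the definition of the sole primary endpoint. As written, the rule analyses each patient's slower attempt at a maximal-speed test; if best was intended, it says the reverse.

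Individual values differ by about 0.95 s between the two readings, or up to 2.12 s over the assumed ICC range. The between-arm estimate would typically move by about 0.09 s (0.19 s at ICC 0.80) against a standard error near 0.67 s, which could matter only for a borderline result. These sizes rest on normal, independent attempt errors, on an SD of 4.2 s for a single attempt, and on using a published reliability coefficient as within-visit agreement. The conflict between rule and scale rests on none of these.

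The documents do not support a claim of bias, of material loss of power, or of an error in the sample size from this source.

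**What to change.** Replace the sentence in the Primary outcome section with:

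> The shorter (faster) of the two TUG times, in seconds with lower meaning better, is analysed at every visit, including preoperative and baseline.

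If average performance is wanted, name the mean of the two times instead; the precision gain is negligible and should not be the reason. If the slower attempt is truly intended, state it as the longer time and justify it. Whichever is chosen, fix it before unblinded analysis so that it cannot depend on the result.

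The cost is one sentence. The TUG is recorded twice, so if both times were kept, the endpoint can be recomputed without new measurements.
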